### Data collection stages and procedures

The study will proceed in three stages at the St James’s Hospital (LTHT) with the dietary intervention and interviews conducted remotely (e.g., participant’s home) (figure 1). All pregnant women with pre-existing T1DM or T2DM are scheduled for regular NHS clinical visits every 2 weeks throughout the pregnancy. Each woman has an assigned diabetes midwife who caseloads her pregnancy and liaises with the rest of the clinical care team. Due to COVID-19 and intermittent lockdowns, pregnant women only attend face-to-face meetings at the clinic when due for a scan (*a dating scan* at 10–12 weeks, an *anomaly scan* at 18–20 weeks and *growth scans* at 26–28, 32–34 and 36 weeks of pregnancy) unless deviated due to complications or early delivery. All women with T1DM and T2DM are currently offered CGM as part of their clinical care. The CGM data are automatically uploaded to a secure, remote clinical database, where it can be securely accessed and downloaded by the clinical team and authorised researchers.

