### Nested cross-over dietary meal intervention within the study

Shortly after their clinical visit at ~18–20 weeks and ~28–34 weeks, participants will be asked to consume standardised breakfast meal replacements in their own home, at breakfast time for 4 days. These will be two different experimental meals (A and B; matched for 400 kcal and 13 g of fat) consumed under free-living conditions. The experimental meals will appear and taste similar but differ in protein quantity which will alter how quickly the glucose in each meal is absorbed into the blood.^22^ One experimental meal will have 20 g of vegan and gluten-free protein powder added, which slows gastric emptying and glucose absorption into the blood to a rate that is comparable with commonly consumed whole-grain breakfast cereals (eg, steel-cut or rolled oats; GI ≈40). The other experimental meal will have no added protein. The experimental meals (labelled A or B) with a drink shaker are stored in a box by the research team in a COVID-19-safe laboratory. Each participant will be assigned to one of six random orders to consume the experimental breakfast meals (AABB, ABAB, BBAA, BABA, ABBA, BAAB) over 4 days using an online randomiser (https://www.random.org/integer-sets/). This will be done by block randomisation to assign 12–13 participants to each of the six possible orders of meal consumption, which the participant will follow for both sets of meals (i.e., ~18–20 and ~28–34 weeks). The participant will only need to pour the powder into the shaker, add cold water to the line marked on the cup (500 mL), and consume within 5 min.

The powder is a nutritionally complete meal replacement in drink form; every meal contains a balance of protein, carbohydrates, essential fats, fibre, plus all 26 essential vitamins and minerals, and phytonutrients. Additionally, the product is low in sugar, lactose-free, contains no nuts or palm oil, and has a long shelf life. The powder is commercially available and is produced in facilities that meet highest quality standards. This product was chosen to minimise time burden for participants and it is free from many commonly avoided food items (i.e., lactose, nuts, gluten and meat).

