Participants will be asked to avoid consuming other foods and drinks (aside from water) for 2 hours, after which they may consume food as usual. However, they are freely permitted to measure their own blood glucose levels at any point and will be advised to manage any hyperglycaemic or hypoglycaemic events, even if this means eating or drinking within 2 hours of the meal. Participants will be asked to inform the research team of any events by email as soon as possible.

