### Quality control

All participants will receive standard clinical care as per NICE guidance, which will minimise researcher bias. The primary outcome measures are based on laboratory measurements and predetermined cut-off values, which the researchers will not be able to influence. We do not foresee significant researcher bias in collecting antenatal and perinatal outcome data because these will be obtained by clinical staff who are independent of the study outcome and from the participants’ medical records. We do not foresee any significant researcher bias in collecting lifestyle records, as standardised and validated questionnaires will be used to obtain this information. Furthermore, all participants will be asked to consume the two standard meals but the order of their consumption will be randomised. We do not foresee any conflict of interests. The data collected will not be used for informing clinical care decisions of specific cases; all the women will continue with their usual clinical care pathway for the duration of their pregnancy, and all women will be free to terminate their participation in the study at any time with no effect on their quality of care.

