## Discussion

The INFORMED clinical trial is double-blinded cross-over randomised clinical trial to evaluate the effect of dietary protein within experimental meals on dysglycaemia in women with pre-existing type 1 or type 2 diabetes. Additionally, we will explore (1) the association between dysglycaemia and maternal and newborn health, and (2) the association between maternal metabolic profiles in early pregnancy with dysglycaemia in later pregnancy, which may provide insights into novel precision therapies for women with DIP.^26^ The identification of dietary mediators of glucose variability will aid in the development of more efficacious and appropriate strategies to control glucose levels and minimise maternal and offspring risks in women with DIP.^12 13 26^

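### Two fixed meal letters and a repeated order leave participant blinding vulnerable, so the coding described does not back the double-blind statement

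*Protocol article*

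**What the plan says.** The relevant rules are spread over several sections of the protocol article.

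- Labels (Nested cross-over dietary meal intervention): "The experimental meals (labelled A or B) with a drink shaker are stored in a box by the research team".
- Orders (same section): each woman is randomised to one of six orders "to consume the experimental breakfast meals (AABB, ABAB, BBAA, BABA, ABBA, BAAB) over 4 days", so each letter occurs twice per set. Blocks "assign 12–13 participants to each of the six possible orders of meal consumption".
- Repetition (same section): the order is one "which the participant will follow for both sets of meals", at about 18–20 and 28–34 weeks.
- Masking (same section): the two meals look and taste alike, but the added protein is meant to change the speed of glucose absorption.
- Own glucose (same section): participants avoid other food for 2 hours, but "they are freely permitted to measure their own blood glucose levels at any point and will be advised to manage any hyperglycaemic or hypoglycaemic events".
- CGM (Data collection stages and procedures): "All women with T1DM and T2DM are currently offered CGM as part of their clinical care". Masking of the readings is not mentioned.
- Primary outcome (Statistical analysis considerations): AUC glucose over the 24 hours after each study meal.
- Blinding: the abstract calls the meals blinded, and the Discussion calls the study a "double-blinded cross-over randomised clinical trial".

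**The concern.** Similar look and taste hide the meals before they are eaten. They do not hide what the meals do afterwards, and here the effect under study is one that the participant can observe in herself. With only two letters, anything learned about a letter on one day carries over to every later day with that letter.

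She does not need to know which letter has the added protein. It is enough that she believes one letter runs higher for her. She could then change food, activity or other self-management on those days and not on the others. That would be a letter-specific co-intervention acting on the primary outcome, in a window of which 24 − 2 = 22 hours follow the fasting period. The estimated protein effect would then mix the meal with the woman's response to her expectation. Because more is known by the second set, the mix could differ between trimesters.

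**Working it through.** The article gives no figure for blinding, so there is none to reproduce. Two checks apply.

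**1. Meals eaten after both letters have been tried.** Inputs: six orders, 4 days per set, 2 sets, same order in both, hence 4 × 2 = 8 breakfasts per woman. A comparison needs at least one A day and one B day.

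| Order | Day on which the second letter first appears | Later meals in set 1 | Meals in set 2 | Total of 8 |
|---|---|---|---|---|
| AABB, BBAA | 3 | 1 | 4 | 5 |
| ABAB, BABA, ABBA, BAAB | 2 | 2 | 4 | 6 |

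Mean over the six orders: (2 × 5 + 4 × 6)/6 = 34/6 = 5.67 of 8, or 71%. The orders are used about equally (76/6 = 12.67, in line with the stated 12–13 per order), so this is also close to the trial average.

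**2. How likely is she to rank the letters correctly?** Let d be the true difference in her glucose between the two meals, divided by her day-to-day SD. With n days per letter, independent days and normal errors, the difference of the two means has standard error SD × √(2/n). So

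P(correct ranking) = Φ(d × √(n/2)).

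The article does not give d; the values below are assumptions.

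| d (assumed) | n = 1 (after the first A and first B) | n = 2 (entering set 2) |
|---|---|---|
| 0 | 50% | 50% |
| 0.25 | 57% | 60% |
| 0.5 | 64% | 69% |
| 1.0 | 76% | 84% |
| 1.5 | 86% | 93% |

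For example, d = 0.5 and n = 1 gives Φ(0.5 × 0.707) = Φ(0.354) = 64%. Guessing alone gives 50%. The letters are therefore learnable if the meal effect is large against day-to-day variation, and barely so if it is small.

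**3. Labels and order together.** While the letters stay, the repeated order adds little, because the letter already identifies the meal. If the letters go but the order is repeated, day 3 of set 2 is the same meal as day 3 of set 1, so the day becomes the label. Both features have to change.

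**The case against.** Several stronger readings are tempting, and the article does not support them.

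- *The double-blind claim is false.* Telling two letters apart is not the same as being told which one has the added protein, and recognition is not shown. With d = 0.25 a woman is close to guessing. Meals are eaten in free-living conditions, and the sets lie 28 − 20 = 8 to 34 − 18 = 16 weeks apart, so she must also remember. This objection stands against the word false, but not against the vulnerability.
- *Three quarters of the meals are unblinded.* 6 of 8 meals follow an earlier meal with the same letter in every order, but a comparison needs both letters. That gives 5 or 6 of 8, and these are meals at risk.
- *One disclosure breaks the code for all.* The article does not say that A is the same meal for every woman, and a report of high glucose after one letter does not identify it.
- *The bias shrinks the effect, most of all in the third trimester.* This is plausible, but nothing in the article establishes it.
- *The Quality control section gives false reassurance.* Its remark about "predetermined cut-off values, which the researchers will not be able to influence" concerns researcher bias. It neither addresses nor dismisses participant behaviour.
- *Repeating the order confounds meal with day.* The mean day of B minus that of A is +2, +1, 0, 0, −1 and −2 over the six orders, which sums to zero. The orders are nearly equally filled, and the model adjusts for meal order.

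Visible letters at home and a visible CGM trace are also inferences. The first is strong, since she has to follow an order; for the second, free self-measurement is enough. Finally, who holds the code may be set out in the full protocol, so its absence from the article is not the point. The point is the labelling and the repeated order, which the article does fix.

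**Conclusion.** Participant blinding is vulnerable as designed, and the double-blind statement in the Discussion is not backed by the coding described. On average 71% of a woman's study breakfasts (5 or 6 of 8) come after she has tried both letters. What share of these is affected cannot be said. It depends on d, which is not given, and on whether women act on what they notice.

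The conclusion assumes that she sees the letter and looks at her own glucose. It does not show that any woman will be unblinded, that the research team is unblinded, or in which direction the result would move. If the meals did not differ at all (d = 0), and beliefs came only from glucose, women would be split evenly over the two letters and the average contrast would not shift. The threat is thus mainly to the size of a real effect. This is a worthwhile, cheap improvement and does not invalidate the trial.

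**What to change.** 1. Label each meal by participant number, set and day only, with no A or B.
2. Draw a fresh random order from the same six for the second set. A mirror image of the first order would not do, since anyone who had worked out set 1 could predict it.
3. Keep the code list with someone who neither contacts participants nor analyses the data.
4. After each set, ask each woman which two days she thought were high protein, and report the answers. A random pick is wholly right 1 time in 6, since there are six possible orders. A better result could come from taste or from the glucose effect itself, so it should be read with care.
5. Describe blinding in the words that the coding and these answers support, naming who is blinded.

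The cost is packing by participant instead of from two stocks, a second column in the randomisation list, and one question per set. The account of the third call says that women are not contacted afterwards, so the second question is best put on a card in the meal box or an online form. No extra patients or visits are needed. If packing is already done, items 4 and 5 can still be adopted.

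The change limits anticipation and does not abolish it. A woman who can tell the meals apart, and knows that each comes twice, can still work out the last day of a set. Correction of glucose after a meal also remains possible. That permission is a matter of clinical care and should stay unchanged.

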### Data management

The research team will assign unique random screening IDs at the recruitment phase. The study ID will be used to pseudonymise (using personal participant identification numbers) and harmonise the data shared by the NHS clinical database (clinical records) with the data collected by the research team at the University of Leeds (ie, questionnaires, metabolite and genetic data). Only the clinical team and authorised members of the research team will be able to link the study ID to the participant. All personally identifiable information will be stored in a password-protected and encrypted database in a secure area.

*Clinical data:* standard care to measure and collect maternal anthropometric, glycaemic, medication, lipid levels, and blood pressure information during routine hospital visits and during and after labour. Offspring anthropometry measures are taken by the direct healthcare team, which is part of routine care. The women will be asked to give consent for the research team to access their clinical records to obtain these data.

*CGM:* standard clinical care in T1DM and T2DM pregnancies; women will be asked to give consent for the research team to access their CGM data. Of the numerous metrics provided by CGM—that is, AUC, mean glucose, coefficient of variation of glucose, MAGE and TIR—AUC will be the primary metric for the study.

*Urine samples:* standard clinical care; we will ask for up to 2.5 mL of any urine not required for clinical analysis to be saved for research use. These samples will be stored for subsequent metabolic analysis. All samples will be stored at the University of Leeds in designated Human Tissue Act-approved and compliant facilities.

*Blood samples:* standard clinical care requires blood samples for analysis. At the time of routine collection at each clinical visit, an additional 10 mL blood will be collected for this study. These blood samples will be stored for subsequent metabolic and genomic analysis (relevant to nutrition/diabetes/pregnancy and fetal growth). All samples will be stored at the University of Leeds in designated and secure facilities.

*Lifestyle questionnaires:* at three time points across pregnancy (~10–12, ~18–20 and ~28–34 weeks’ gestation), a designated member of the research team will call (phone or video) the participant to complete the questionnaires on physical activity, sleep quality/patterns and habitual mealtime habits.

*Dietary records:* at two time points across pregnancy (~18–20 and ~28–32 weeks of gestation), each participant will be asked to record their diet for 3 days (2 week days, 1 weekend day) using a validated online semiquantitative food frequency questionnaire (myFood24), which estimates dietary intake data (i.e., macronutrients, micronutrients and vitamins for up to 220 nutrients) according to McCance and Widdowson (seventh edition) and branded items that offer nutritional data.^23^ Briefly, the data are provided to researchers as a spreadsheet with anonymised identifiers for each participant that can be directly imported into R for analysis. The performance of myFood24 and telephone-based 24-hour dietary recall is in agreement (interclass correlation 0.4–0.5). ^23^

#### Outcomes of interest

The primary outcome of interest is CGM glucose data, with AUC glucose as the primary CGM metric of interest. Secondary outcomes of interest are associations between metrics of dysglycaemia during pregnancy with maternal outcomes (e.g., gestational weight gain, pre-eclampsia, hypertension, mode of birth, birth trauma, preterm delivery and metabolism) and infant outcomes (e.g., birth weight, height, preterm delivery, mortality, birth trauma, hypoglycaemia, congenital malformation, head and abdominal circumference, perinatal morbidity), and the moderating effects of genetics, metabolism, and diet and lifestyle. All secondary analyses are considered exploratory.

### Statistical analysis considerations

All standard CGM metrics will be calculated, with AUC glucose as the primary CGM metric (mean±SD). The primary analysis will be the effect of dietary protein on AUC glucose for the 24-hour window immediately after each study meal. The analysis will be constructed as pairwise linear model with study meal (0=low protein, 1=high protein) regressed against 24-hour mean AUC glucose and adjusted for study parameters (e.g., randomised meal order) and participant covariates (e.g., maternal age, ethnicity, parity, BMI, gestational age, physical activity and sleep quality). Statistical significance will be set at p<0.05, where a p<0.05 for study meal will suggest a significant effect of dietary protein on 24-hour postprandial AUC glucose. The direction and significance of covariates will be investigated to identify study and participant mediators of the association. Statistical analysis will be conducted in R studio and SPSS (Ver. 29+).

Secondary research objectives include (1) the association between dysglycaemia and maternal and newborn health, and (2) the association between maternal diet in early pregnancy with dysglycaemia during pregnancy. These analyses will also be performed using regression models adjusted for covariates, with the assessment of early diet on longitudinal changes in dysglycaemia also adjusted for time points of AUC (i.e., mixed-model). The association between early maternal diet and AUC will be performed using three distinct dietary metrics (calculated from myFood24):

1. Overall diet quality

The association between diet quality and dysglycaemia will be assessed using an overall diet quality score.^24^ This scoring method has been modified and used previously to assess maternal diet quality in a multiethnic prospective birth cohort.^25^ The modified Alternative Healthy Eating Index (mAHEI) score is calculated using the following method; an individual will receive 10 points for each of the following food categories when they consume above or below a threshold of: ≥5 servings of vegetables, ≥4 servings of fruits, ≥1 serving of nuts or soy proteins, ≥3 servings of whole grains, a ratio of ≥4 servings of fish to 1 serving of meat and eggs, and ≤0.5 servings of less-healthy foods (i.e., fried foods and processed meats). Intermediate intake is scored proportionally between 0 and 10. The maximum mAHEI score is 60; the higher the score, the more healthful the participant’s diet.

2. Macronutrient

Daily macronutrient consumption (total carbohydrates, proteins and fats) and markers of GI quality (fibre, sugars) will be adjusted for energy and regressed against CGM measures of dysglycaemia. Doing so will allow for the contribution of individual macronutrients on glycaemic measures to be evaluated.

3. Cardinal foods

Partial least squares will be used to identify foods that are more commonly observed in participants with favourable or unfavourable glycaemic control (identified above/below median for glycaemic measures). These foods will then be investigated for their association with measures of dysglycaemia using a regression model.

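### The primary model does not say how pairing within a woman enters, although each woman gives up to eight correlated 24-hour windows; read literally as ordinary regression, its standard errors are wrong.

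*Protocol article*

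**What the plan says.** **Design** (Nested cross-over dietary meal intervention within the study). Participants "consume standardised breakfast meal replacements in their own home, at breakfast time for 4 days", two of each meal, in one of six randomised orders, "which the participant will follow for both sets of meals (i.e., ~18–20 and ~28–34 weeks".

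**Primary model** (Statistical analysis considerations). The outcome is "AUC glucose for the 24-hour window immediately after each study meal". The model is given as: "The analysis will be constructed as pairwise linear model with study meal (0=low protein, 1=high protein) regressed against 24-hour mean AUC glucose". It is adjusted for study parameters, with randomised meal order as the example, and for "participant covariates (e.g., maternal age, ethnicity, parity, BMI, gestational age, physical activity and sleep quality". The conclusion rests on p<0.05 for the meal term. The direction and significance of the covariates will also be examined, to identify mediators.

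**Secondary model** (same section). The early-diet analysis is described "with the assessment of early diet on longitudinal changes in dysglycaemia also adjusted for time points of AUC (i.e., mixed-model". This is the only place where a model for repeated measures is named.

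**The concern.** The meal comparison is made within women, while age, ethnicity, parity and randomised order vary only between women. A model without a participant effect uses one residual variance for both kinds of comparison and misstates both. Between-woman variance stays in the error of the meal contrast, which gives up the cross-over's main advantage. For the traits, eight correlated rows are counted as eight independent ones.

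The word *pairwise* may be meant to solve this, but it is not defined. A 0/1 meal regressor entered beside woman-constant adjusters describes a row-level model, not a model of differences. At stake are the power of the only confirmatory test (the protocol calls all secondary analyses exploratory) and the credibility of the covariate findings it plans to interpret.

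**Working it through.** **Inputs from the protocol article.** Rows per woman: 4 meals × 2 occasions = 8, four of each meal. Number of women: 63 before attrition. Alpha: 0.05, taken as two-sided. The ICC of the 24-hour AUC is not given; a range of 0.1 to 0.7 is assumed, with total variance set to 1.

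**The plan's own figure.** The 63 women for power 0.90 could not be reproduced from the stated inputs. R²=0.38 with one predictor needs 20, a correlation of 0.38 needs 69, and a paired t-test with a standardised difference of 0.41 needs 65. The G*Power settings, a standard deviation and a within-woman correlation are not stated. The target of 76 is 63 × 1.2 = 75.6. Nothing below depends on how 63 was obtained.

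**Formulas (random intercept, N women, eight rows each).**
- Meal: true variance (1−ICC)/(2N); ordinary regression reports 1/(2N). Reported/true SE = √(1/(1−ICC)).
- Woman-constant covariate: true variance is proportional to (1+7·ICC)/(8N); ordinary regression reports 1/(8N). Reported/true SE = √(1/(1+7·ICC)).

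Example at ICC 0.5: √(1/0.5) = 1.41 for meal and √(1/4.5) = 0.47 for the covariate.

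**Results.** SE ratios are closed form. Rejection rates and power are simulated: 63 women, six orders repeated at both occasions, 3000 runs, order in the model. Power assumes a meal effect of 0.2 total SD.

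| ICC (assumed) | Meal SE ratio | Meal type I error | Covariate SE ratio | Null covariate rejected | Power, ordinary vs paired |
|---|---|---|---|---|---|
| 0.1 | 1.05 | 3.9% | 0.77 | 13% | not run |
| 0.3 | 1.20 | 1.9% | 0.57 | 28% | 64% vs 75% |
| 0.5 | 1.41 | 0.6% | 0.47 | 39% | 67% vs 87% |
| 0.7 | 1.83 | 0.1% | 0.41 | 44% | 72% vs 98% |

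The paired analysis kept meal type I error at about 5% throughout.

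**Where the directions change.**
- *Meal effect differing between women, with SD τ.* Reported/true SE = √((1+τ²/4)/(2τ²+1−ICC)). This exceeds 1 only if τ² < ICC/1.75, that is, 0.57 × ICC. At ICC 0.5 and τ=0.7 it is √(1.1225/1.48) = 0.87 (0.85 simulated), and simulated type I error is about 10%.
- *Covariates that change between visits.* For gestational age at ICC 0.5 under a random intercept alone, the SE is too wide (ratio 1.40). With woman and woman-by-visit components of 0.3 each it is too narrow (0.78).
- *Duplicates averaged before analysis* (one reading of *mean AUC*). Averaging raises the ICC of the rows. With a per-meal ICC of 0.5, averaging pairs leaves 4 rows with ICC 0.5/0.75 = 0.67; the covariate ratio is √(1/(1+3×0.67)) = 0.58. Averaging all four leaves 2 rows with ICC 0.5/0.625 = 0.80 and ratio √(1/1.8) = 0.75. Both are milder than 0.47. The meal SE does not benefit: √(1/(1−ICC)) becomes 1.73 and 2.24.

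**Order in a within-woman difference.** A woman's high-minus-low difference contains a day contrast fixed by her order: 2 days for AABB and BBAA (opposite signs), 1 day for ABAB and BABA, none for ABBA and BAAB. With an assumed trend of 0.28 SD per day, the mean squared contrast is 0.28² × (4+1+4+1+0+0)/6 = 0.131. At ICC 0.5 the SE of the mean difference is √((0.25+0.131)/63) = 0.078 without order and √(0.25/63) = 0.063 with it.

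**The case against.** The strongest reply is that, in a cross-over, *pairwise* most naturally means paired within a woman. The adjustment lists are open examples, and random-effects detail normally belongs in an analysis plan that is not shown here. Part of this stands: the article does not exclude a participant effect, so it cannot be said that the sponsor will fit ordinary regression. It does not dispose of the point. The article states the regressors, threshold and decision rule of the primary model, and names a mixed model one paragraph later for another analysis only. The model as written has to be restated under either reading.

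A reader might also infer the following, which the documents do not support.
- *That every covariate SE is too narrow and the meal SE always too wide.* The first holds for woman-constant covariates and the second only when the meal effect varies modestly between women.
- *That under paired differences the listed adjustment does nothing, so order should be dropped.* Order removes day effects from the differences, as shown above. Traits in a difference regression test whether the meal effect varies with them, which is close to the protocol's stated interest.
- *That gestational occasion is ignored.* Gestational age is a listed covariate and largely separates the two occasions. Day is also balanced by design: across the six orders each meal falls on each day three times.
- *That pre-meal glucose must be added.* It corrects no error. The article states no washout between the four days, so the value on days 2 to 4 may carry over from the previous study meal.

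**Conclusion.** The point holds as a fault in how the primary model is specified. Fitted literally, the model gives wrong standard errors for the meal test and for the covariate tests. Under a random intercept the meal test is conservative, so the harm is lost power and a positive meal result would stand. That reassurance fails if women differ strongly in their response to the meals. The inflated false-positive rates concern woman-constant covariates, not the meal conclusion. They matter because the protocol says it will interpret covariate significance.

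The size depends on assumptions about the ICC, the 0.2 SD effect and the spread of meal effects, none of which the article gives. At ICC 0.1 the meal SE is only 5% too wide. Averaging duplicates lessens the covariate distortion but not that of the meal SE.

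**What to change.** Define *pairwise* and state the primary model in one of two forms.

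1. A linear mixed model with one row per study meal; fixed effects for meal, day within set (1 to 4) and occasion (or gestational age); random intercepts for woman and woman-by-occasion; and a random meal effect considered.
2. An explicit within-woman high-minus-low difference, adjusted for randomised order. Order and any covariates should be centred so that the intercept is the average meal effect. With complete data this is essentially equivalent.

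Say whether duplicates are averaged. Interpret covariate tests only from the chosen model. Neither pre-meal glucose adjustment nor dropping order is required.

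The cost is one paragraph in the protocol or analysis plan, written before the data are analysed. Data, visits and software are unchanged.
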